## STUDY OBJECTIVES

### Objectives

The primary objective is to determine whether 15% DEET repellent used in the evening can reduce malaria incidence. Secondary objectives are to determine whether the intervention has an effect on fevers and dengue, Japanese Encephalitis (JE) and scrub typhus seroconversion. The trial will also monitor lotion acceptability and any occurrence of adverse events.

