### Outcomes

The primary outcome measure will be the incidence of malaria defined as a positive rapid diagnostic test (RDT) result. Secondary outcomes will be all-cause fevers self reported via monthly questionnaires and seroconversion of dengue, JE and scrub typhus measured by ELISA test on dried bloodspots taken during baseline and exit surveys.

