## STATISTICAL CONSIDERATIONS

### Sample Size Calculation

An initial target of 1,000 households was based on the power calculation below (Table 3). The only reliable clinical data from the study area at the time was 32% prevalence of *P. falciparum* from village surveys during September. The incidence over 9 months sampling was estimated to be 2-6%. Hill *et al.* [23] found 80% reduction in cases in their repellent group and Rowland *et al.* (2004b) found a 44% reduction in *P. falciparum*; therefore a 30-50% reduction was used in the calculations.

Sample sizes were recalculated following the first year’s data collection which found a 0.7% incidence of malaria. A sample size of 633 households per arm would therefore be necessary to detect a 50% intervention effect with 95% significance and 80% power. Non-compliance in the first year was around 27%, so the sample size was adjusted to 804 households per arm.

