### Table 4. Revised sample size calculation following first year of data collection (giving a firmer estimate of malaria incidence), calculations are for different scenarios of effect with 95% significance and 80% power

| Assumed Incidence | Intervention Effect | Coefficient of variation (K) | Households Per Arm | Increase 27%  (Loss From Non-Compliance) |
| --- | --- | --- | --- | --- |
| 0.010 | 50% | 0.25 | 948 | 1204 |
| 0.015 | 50% | 0.25 | 633 | 804 |
| 0.020 | 50% | 0.25 | 476 | 605 |
| 0.010 | 40% | 0.25 | 1579 | 2006 |
| 0.015 | 40% | 0.25 | 1054 | 1336 |
| 0.020 | 40% | 0.25 | 792 | 1006 |
| 0.010 | 30% | 0.25 | 2982 | 3787 |
| 0.015 | 30% | 0.25 | 1991 | 2529 |
| 0.020 | 30% | 0.25 | 1495 | 1899 |

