## DATA HANDLING AND RECORD KEEPING

### Data Analyses and Handling

Only the consent forms will contain personal information (names) and these will be stored for the length of the trial in a locked filing cabinet in the project office in Vientiane. Number codes will be used to identify participants during baseline and monthly surveys. Data will be entered into a password protected Microsoft Access database.

The initial analysis will be performed according to intention-to-treat. This will include all participants who were recruited to the trial and gave every monthly RDT result. An additional per protocol analysis will be carried out. This will include only those participants who slept under a bed net and used the lotion in the evenings at least 90% of the time. Positive cases will be subsequently excluded from the trial due to the possibility of them testing positive in later months from the same episode.

Data from both arms from baseline surveys will be compared by ANOVA. Comparison of *P. falciparum*, *P. vivax* and fever incidence between the trial arms will be carried out by poisson regression adjusted for intracluster (household) variation by random effects methods. Comparison of seroconversion for dengue, Japanese Encephalitis and scrub typhus between trial arms will be done using a chi-squared test on numbers seroconverted or not seroconverted over the course of the trial.
An assessment of compliance will be carried out looking in particular at repellent and placebo use and LLIN use. Adverse events in children under 12 years and in participants over 12 years will also be assessed.

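### The primary outcome, malaria by any positive RDT, is missing from the listed outcome comparisons, and no species result is named as deciding the trial

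*Protocol*

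**What the plan says.** The Objectives and Outcomes sections of the protocol agree with each other. The objective reads: "The primary objective is to determine whether 15% DEET repellent used in the evening can reduce malaria incidence". The outcome reads: "The primary outcome measure will be the incidence of malaria defined as a positive rapid diagnostic test (RDT) result". Neither names a species. The Outcomes section lists fevers and seroconversion as secondary; it does not mention species-specific malaria.

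The revised sample size follows the same line. The Sample Size Calculation section says: "Sample sizes were recalculated following the first year’s data collection which found a 0.7% incidence of malaria". Its conclusion is: "A sample size of 633 households per arm would therefore be necessary to detect a 50% intervention effect with 95% significance and 80% power". The Table 4 row behind that figure is "0.015 | 50% | 0.25 | 633 | 804" (incidence, effect, K, households per arm, households after the 27% increase). No species is named here either.

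Data Analyses and Handling is the only section that states how outcomes will be compared between arms. It says: "Comparison of *P. falciparum*, *P. vivax* and fever incidence between the trial arms will be carried out by poisson regression". The model is to carry a random effect for household, and the section adds a chi-squared test for seroconversion. It also says that participants who test positive leave the trial from then on.

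**The concern.** The analysis section names its model, its clustering adjustment and its outcomes, so it does fix the analysis. It fixes it on endpoints other than the declared primary one. An analyst who followed that section as written would fit a *P. falciparum* model and a *P. vivax* model, and would not fit the model that answers the primary objective.

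Two things are at stake. First, the two species results may disagree, and the protocol does not say what would then be concluded. Its own Background shows that this can happen: in the household trial in a refugee camp in Pakistan, the odds of *P. falciparum* fell by 44% while no effect was found on *P. vivax*. Second, the sample size was worked out for the combined rate. If both species occur, each has a lower rate than the two together, so each species comparison has less power than the combined one.

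**Working it through.** **Comparing the sections**

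| Section | Malaria endpoint |
| --- | --- |
| Objectives | malaria incidence, no species |
| Outcomes (primary) | any positive RDT, no species |
| Sample Size Calculation, revised, and Table 4 | malaria incidence, no species |
| Data Analyses and Handling | *P. falciparum*; *P. vivax* |

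The last row does not match the other three.

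**Inputs for the power check**
- Control incidence r0 = 0.015, effect 50% (so r1 = 0.0075) and K = 0.25: the Table 4 row that gives 633 and 804.
- Two-sided 5% and 80% power: from the stated 95% significance and 80% power, with two-sided as my reading. (1.960 + 0.842)² = 7.849.
- m = 5 people per household: the minimum in Participant and Household Eligibility. The protocol does not say which cluster size was used.
- Species share of cases: not in the protocol. Assumed, and shown as a range.

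**Reproducing the plan's figure**

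The unmatched cluster formula for rates is

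c = 1 + 7.849 × [(r0 + r1)/m + K²(r0² + r1²)] / (r0 − r1)²

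- (0.015 + 0.0075)/5 = 0.0045
- 0.0625 × (0.000225 + 0.00005625) = 0.0000176
- (0.0045 + 0.0000176)/0.00005625 = 80.31
- c = 1 + 7.849 × 80.31 = 631.4, against the stated 633

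With m = 5 the same formula reproduces all 19 rows of Tables 3 and 4 within 3%. The stated 804 is 633 × 1.27.

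**Power for one species**

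For a 50% effect with K = 0.25 and m = 5, the bracket divided by (r0 − r1)² simplifies to V = 1.2/r0 + 0.3125. Power is Φ(√[(c − 1)/V] − 1.960). A species with share s of cases has r0 = 0.015 × s.

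At 633 households per arm, c − 1 = 632:

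| Share of cases | r0 | V | √(632/V) | Power |
| --- | --- | --- | --- | --- |
| 100% (all malaria) | 0.0150 | 80.31 | 2.805 | 80% |
| 90% | 0.0135 | 89.20 | 2.662 | 76% |
| 70% | 0.0105 | 114.60 | 2.348 | 65% |
| 50% | 0.0075 | 160.31 | 1.986 | 51% |

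The rarer species fares worse: 34% power at a 30% share and 14% at a 10% share. For 80% power on one species, the same formula asks for 702, 901 and 1,260 households per arm at shares of 90%, 70% and 50%.

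**The same check at 804 per arm, full compliance**

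Here c − 1 = 803. Power for all malaria is 88.5%. At a 79% share, r0 = 0.01185, V = 101.58 and √(803/101.58) = 2.812, so power is 80.3%. At shares of 70% and 50% it is 75% and 61%. This basis treats the 27% increase as spare capacity, although it was added to cover non-compliance. The 633 basis is therefore the fairer one.

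I used 0.015 because that row produces 633 and 804. The text beside it cites 0.7% ("which found a 0.7% incidence of malaria"). That mismatch is a separate matter and would lower every power figure here.

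**The case against.** The strongest reply is that the hierarchy is already settled. The Outcomes section names one primary outcome, and no section calls either species result primary or co-primary. On that reading the analysis section only supplies the model for incidence outcomes and says that malaria will be reported by species. The statistical analysis plan, which is not shown, could add the combined comparison. This has some force: the protocol does not rule out the combined analysis, so a reader who concludes that the effect on malaria will never be estimated goes beyond the text. What remains is that the one section listing outcome comparisons omits the primary outcome and lists two other malaria endpoints in its place. That is a mismatch between sections, not a detail left for later.

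Two stronger readings are tempting, and the protocol does not support either.

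- A reader might infer a false-positive rate near 10%. For two independent tests at 5% it is 1 − 0.95² = 9.75%, but only if success on either species counted as success of the trial. The protocol states no such rule, and a multiplicity rule may properly sit in the analysis plan.
- A reader might infer that neither species comparison can reach the stated 80% power. At 804 per arm with full compliance, a species with about 79% or more of cases does reach it.

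It is also fair to note that the initial calculation drew partly on *P. falciparum* data (32% prevalence, 44% reduction). The statement that the sample size is for malaria of any species applies to the revised calculation, which replaced it.

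**Conclusion.** The point holds as an internal mismatch. The primary outcome as defined does not appear among the stated comparisons, and no species result is identified as deciding the trial. This rests on the wording alone.

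The cost in power depends on a species split that the protocol does not give. At 633 per arm, 80% for all malaria becomes 76%, 65% or 51% for a species with 90%, 70% or 50% of cases. The direction is certain if both species occur and the effect is the same 50%. These figures also assume incidence 0.015, K 0.25 at every share and 5 people per household. No inflated error rate is established. The matter should be corrected, but it does not undermine the design.

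**What to change.** In Data Analyses and Handling, state that the single primary test compares the incidence of first RDT-positive malaria of any species between arms, using the household random-effects Poisson model already named, at two-sided 5%. State that *P. falciparum* and *P. vivax* incidence are secondary estimates, reported with confidence intervals. Using the first positive of any species also fits the rule that positive cases leave the trial, since a participant positive for one species is no longer followed for the other.

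The cost is one or two sentences. No new data, visits or households are needed; the species results become secondary. The alternative, making the species results co-primary, would mean rewriting the primary outcome, dividing the 5% and redoing the sample size. At 633 per arm and 2.5% for each species, power for a species with 90%, 70% or 50% of cases would be 66%, 54% or 40%.

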## PROTOCOL SUMMARY

Population

Approximately 8,000 rural agricultural workers and children aged from 6 to 60 years, resident in 126 villages in Sekong and Attapeu Provinces in southern Lao PDR.

Sites

One

Study Duration

March 2009 to Feb 2012

Subject Participation Duration

Either 7 months from June to December 2009, or 9 months from April to December 2010

Interventions

1. A single Long-lasting insecticide treated net (PermaNet®2.0, deltamethrin 55mg/m2, mesh 25 holes/cm2) for every 1.5 people in the household

2. 15% DEET lotion or a placebo lotion (both supplied by SCJohnson)

Objectives: The aim of the study is to evaluate the efficacy of 15% DEET insect repellent to reduce malaria incidence in rural populations living in southern Lao PDR.

Study Design: The study will take place in Attapeu and Sekong Provinces in southern Lao PDR and will involve 8000 subjects clustered by household. Participants will be primarily recruited amongst rural agricultural populations who often work and sleep away from the village during the wet season. Either a DEET or placebo lotion will be provided for participants to use every evening. All participants will be supplied with long lasting insecticide treated nets (LLINs). Data collection will take place during June to December of 2009 and April to December of 2010. Malaria cases will be identified through active case detection using RDTs (rapid diagnostic tests) at baseline and at monthly intervals post-intervention. Secondary outcomes are all-cause fevers self reported via monthly questionnaires, and dengue, JE and typhus IgM/IgG from bloodspots collected at baseline and exit.

ClinicalTrials.gov Identifier: NCT00938379

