### Randomisation

Randomisation to repellent or placebo lotion will take place at the household level and is stratified by village. All the households in a village will be assigned to either group 258 or 305 (manufacturer codes of repellent and placebo lotions) during the baseline survey. District health workers who recruited and carried out the baseline survey labelled straws with the group codes which the heads of households then picked.

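### Village is the stratification factor but is absent from the stated Poisson model for malaria and fever; the likely cost is a mildly conservative test, not bias

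*Protocol*

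**What the plan says.** The Randomisation section sets the design: "Randomisation to repellent or placebo lotion will take place at the household level and is stratified by village". The Protocol Summary describes the participants as "resident in 126 villages in Sekong and Attapeu Provinces in southern Lao PDR", so there are about 126 strata. In practice district health workers "labelled straws with the group codes which the heads of households then picked". The section does not say whether equal numbers of straws for each code were prepared in each village.

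The primary endpoint is in the Outcomes section: "The primary outcome measure will be the incidence of malaria defined as a positive rapid diagnostic test (RDT) result". Data Analyses and Handling then fixes the comparison of *P. falciparum*, *P. vivax* and fever between arms as "poisson regression adjusted for intracluster (household) variation by random effects methods". Household is the only adjustment named. Seroconversion is to be compared by a chi-squared test on counts, with no adjustment for household or village.

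The sample size also treats the household as the cluster, with a coefficient of variation K of 0.25 or 0.30. It takes no credit for stratification.

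**The concern.** When allocation is balanced within strata, a difference in malaria risk between villages affects both arms equally and drops out of the treatment contrast. A model that does not know about villages cannot use this. Households in a high-transmission village look like households with high individual frailty, and their shared excess goes into the household random-effect variance. The reported standard error then exceeds the true sampling variability of the estimate, and the test rejects less often than its nominal level.

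What is at stake is precision. At 1.5% control incidence, five participants per household and 804 households per arm, a 50% effect means about 804 × 5 × 0.015 = 60 control cases and 30 DEET cases. Fever uses the same model. If fever is commoner, Poisson noise masks less of the village variation and the same omission costs more.

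**Working it through.** **Inputs.** From Tables 3 and 4 and the sample size text: control incidence 0.015, effect 50%, K = 0.25, 80% power, alpha 0.05 (taken as two-sided). From the eligibility section: at least five participants per household (five used). From the summary: 126 villages, hence 2 × 804 / 126 ≈ 12.8 households per village. No between-village CV is given. The only geographic contrast in the background is 101 versus 163 per 1,000 between the two provinces, an unweighted CV of 31/132 ≈ 0.23. Village CV is therefore an assumption, shown over 0.25 to 2.0.

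**Reproducing the plan's figure.** The row is "0.015 | 50% | 0.25 | 633 | 804". The unmatched cluster-rate formula is

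c = 1 + (1.96 + 0.8416)² × [(λ0 + λ1)/y + K²(λ0² + λ1²)] / (λ0 − λ1)²

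With λ0 = 0.015, λ1 = 0.0075, y = 5 and K = 0.25, the bracket is 0.0045 + 0.0000176 = 0.0045176. Dividing by 0.00005625 gives 80.31, and c = 1 + 7.849 × 80.31 = 631.4, against 633 stated. Then 633 × 1.27 = 804. With K = 0 the formula gives 628.9. At the plan's own K, all between-household variation, including any village part, adds about 2.5 households per arm. At 633 per arm it costs about 0.2 power points (80.3% to 80.1%). With 5 × 0.015 = 0.075 expected cases per control household, Poisson noise dominates.

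**Standard error, closed form.** With μ expected cases per household, household CV k_h and village CV k_v, the variance per household on the log scale is 1/μ + k_h² when village is accounted for. Ignoring village adds k_v²(1 + k_h²). At no effect, μ = 0.075 and k_h = 0.25:

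- Base: 13.333 + 0.0625 = 13.396.
- k_v = 0.5 adds 0.266; SE ratio √(13.662/13.396) = 1.01.
- k_v = 1.0 adds 1.0625; ratio 1.04.
- k_v = 1.5 adds 2.391; ratio 1.09.
- k_v = 2.0 adds 4.25; ratio 1.15.

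Under a 50% effect the base summed over arms is 13.333 + 26.667 + 0.125 = 40.125. At k_v = 2.0 the ratio is √(48.625/40.125) = 1.10.

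**Simulation, arms balanced within village.** 804 households per arm, 126 villages, five per household, 1.5% control incidence, household CV 0.25, 800 runs per setting. A gamma household random-effect Poisson model is compared with a village-stratified conditional Poisson model.

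| Village CV | Power, household only | Power, village-stratified | Loss (points) | Type I error, household only |
| --- | --- | --- | --- | --- |
| 0.25 | 88.4% | 89.1% | 0.7 | 3.8% |
| 0.5 | 87.4% | 87.9% | 0.5 | 3.8% |
| 1.0 | 88.2% | 89.5% | 1.3 | 4.2% |
| 1.5 | 85.5% | 88.1% | 2.6 | 3.2% |
| 2.0 | 82.2% | 88.0% | 5.8 | 2.9% |

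The stratified model's type I error is 4.2% to 5.2% over these rows. With 800 runs the simulation error is about 1.1 points on a power near 88% and 0.8 points on a 5% level, so the first rows show no clear difference. At CV 2.0, under the 50% effect, the household-only model's mean standard error is 0.250 while its estimates have a standard deviation of 0.228 (ratio 1.10, as in the closed form). The stratified model gives 0.228 and 0.227. The estimate itself is not less precise; its reported error is too large.

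**Simulation, arms not balanced within village.** Household-only type I error is 5.0%, 5.4% and 5.0% at CV 0.25, 1.0 and 2.0. Power, household-only versus stratified, is 89.6% versus 86.1%, 87.4% versus 87.4%, and 81.0% versus 86.6%. Stratification gains only at the high CV.

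**Lower malaria incidence.** The sample size text reports the "first year’s data collection which found a 0.7% incidence of malaria", with no arm stated. Using 0.7% purely as a control-rate scenario (μ = 0.035), the SE ratio is about 1.02 at CV 1.0 and 1.07 at CV 2.0.

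**Fever.** The documents give no fever rate. Assume 0.2, 0.5 or 1.0 episodes per person (μ = 1, 2.5, 5) and carry over k_h = 0.25. At village CV 0.5 the SE ratios are √(1.328/1.0625) = 1.12, √(0.728/0.4625) = 1.25 and √(0.528/0.2625) = 1.42. At CV 0.25 they are 1.03, 1.07 and 1.12.

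**The case against.** The strongest reply is that a household random effect matches the unit of randomisation and gives a valid test, and that an analysis plan not shown here could add stratification factors. The first part stands: nothing here makes the stated test invalid. The second stands only in part. The protocol is not silent on adjustment: it names the clustering term and leaves out the one factor it stratified by.

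It can also be said that the effect is negligible on the plan's own inputs. For malaria this is right at K = 0.25. A material loss needs a village CV well above 1, which is plausible for focal transmission but not documented. Nor was the recommended nested random-intercept model itself simulated; the comparator was a conditional stratified model.

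Four stronger readings are tempting and not supported:

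- That the trial is underpowered because of this omission. The sample size already counts between-household variation at K = 0.25 as error and takes no credit for stratification. In the simulation at 804 per arm, household-only power stays above 80% at every CV tried. That simulation assumes the full 50% effect and does not model non-compliance.
- That type I error is inflated because whole villages received one code. One sentence in the Randomisation section could be read that way, but the sentence before it makes the household the unit.
- That the two seasons used different villages, so that omitting village also mixes seasons. The Study Schedule lists village selection in both years, and recruitment included Attapeu both times. Separate village sets are not stated.
- That 0.7% is the control-arm rate. It is reported only as first-year incidence.

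**Conclusion.** The mismatch is real: village is the stratification factor and the stated Poisson model for malaria and fever omits it. If the straws gave balance within villages, which the protocol does not state, the household-only standard error is somewhat too large and the test mildly conservative, with no bias. For malaria the loss is small unless village heterogeneity is large: a village CV of 1.5 or more is needed before it reaches about 3 power points. For fever the cost could be material at a modest village CV, but this rests on assumed fever rates. If there was no balance within village, the test keeps its nominal size and the case for the village term in the malaria model is weaker. The change is worth making because it aligns analysis with design at almost no cost, not because the primary result is at risk.

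**What to change.** In Data Analyses and Handling, specify the malaria and fever models as Poisson regression with arm as a fixed effect and random intercepts for village and for household within village. Conditioning on village as a stratum is an acceptable alternative. The random intercept is preferable because many villages may have few or no cases, and because the conditional model lost power at low village CV when arms were unbalanced (86.1% versus 89.6%). State also whether equal numbers of each code were placed among the straws in each village.

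Seroconversion is planned as a chi-squared test, so there is no model to extend. If that comparison is to reflect the design, replace it with a test stratified by village that also allows for household clustering.

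The cost is one extra variance component. Randomisation was done within villages, so village should already be recorded. With few events the village variance may be estimated near zero; the text should say in advance how that case is handled, for example by reverting to the household-only model.

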## PARTICIPANT AND HOUSEHOLD ELIGIBILITY

Participants will be on primarily recruited amongst rural agricultural workers that often work and sleep overnight away from the village during the wet season. Households must enrol at least five eligible participants to enter the trial. Participants must be aged 6-60 years to take part in the trial.

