### Recruitment and Baseline Survey

Recruitment will take place in May 2009, when 300 households will be recruited from Attapeu province, and in April 2010, when 1,300 households will be recruited from both Attapeu and Sekong provinces. Participants will be recruited as volunteers from meetings with village members and local health team staff where the study will be described in full with opportunity for questions. Individuals that wish to take part will also receive this information in writing and sign a consent form to confirm they understand the trial, including the possibility they may receive the placebo lotion. A maximum of 25% of households will be recruited from any village in order to overcome diversion of bites to non-repellent users. In addition district health staff will be responsible for ensuring that study houses contain at least five eligible participants (if the household is bigger, more can be recruited), and that study houses are distributed throughout the village, the rule being that study houses should be a minimum of 10m apart. The baseline survey is scheduled for the same time as recruitment, May 2009 and April 2010. The questionnaire, estimated to take 30 minutes, will collect basic information on wealth indicators and current malaria prevention behaviour for the household and individual information on malaria exposure.

Households will be randomly assigned to one of the treatment groups and supplied with three 100ml bottles per person per month to allow for 10ml use per day as well as sufficient LLINs for the whole household, including non-participants (sufficient LLINs defined as one net for every 1.5 persons in the household, plus another for use away from home). District health staff will demonstrate how to use the lotion and explain that it should be used every evening. Participants will also be encouraged to use the lotion during the day if they notice biting.

A bloodspot will also be taken from each participant and stored on filter paper for laboratory analysis for dengue, JE and typhus. Analysis will ideally take place in Laos if facilities can be found, but if this is not possible the bloodspots will be transported to the UK or France for testing.

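### Seroconversion is to be compared by an ordinary chi-squared test on individuals although households are randomised, so its p-values are likely too small

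*Protocol*

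**What the plan says.** The protocol's Randomisation section states: "Randomisation to repellent or placebo lotion will take place at the household level and is stratified by village". On cluster size, Participant and Household Eligibility says "Households must enrol at least five eligible participants to enter the trial", and Recruitment and Baseline Survey adds that "if the household is bigger, more can be recruited". The Protocol Summary describes a trial that "will involve 8000 subjects clustered by household".

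Under Outcomes, the secondary outcomes include "seroconversion of dengue, JE and scrub typhus measured by ELISA test on dried bloodspots taken during baseline and exit surveys".

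Data Analyses and Handling then treats the outcomes in two ways. *P. falciparum*, *P. vivax* and fever are to be compared by "poisson regression adjusted for intracluster (household) variation by random effects methods". In the next sentence, the comparison of seroconversion for the three other infections "will be done using a chi-squared test on numbers seroconverted or not seroconverted over the course of the trial". No other section adds a household adjustment for seroconversion.

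**The concern.** A chi-squared test on counts of people takes its variance from independent individuals. Here all participants in a household share one allocation, one dwelling and much of their exposure to vectors. If seroconversion clusters within households, the difference between arms varies more than the test assumes, and the test rejects a true null hypothesis more often than its nominal 5%.

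The protocol recognises this dependence in its sample size, through a between-household coefficient of variation, and in its malaria and fever models. It drops it for seroconversion without giving a reason. The test is named in the text, so this is a stated choice and not a detail left to a later analysis plan. At stake is an unreliable claim of benefit against any of three infections, each tested in the same way.

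**Working it through.** **1. Is the design planned as clustered by household?** Inputs from Table 4 (80% power, 95% significance, taken as two-sided 5%) are the row "0.015 | 50% | 0.25 | 633 | 804", that is, incidence 0.015, effect 50%, k = 0.25, and 633 households per arm, or 804 after the 27% increase. I assume y = 5 person-units per household and use the standard formula for comparing rates between clusters:

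c = 1 + (1.960 + 0.842)² × [(λ0 + λ1)/y + k²(λ0² + λ1²)] / (λ0 − λ1)²

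With λ0 = 0.015 and λ1 = 0.0075:

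c = 1 + 7.849 × [0.0225/5 + 0.0625 × 0.00028125] / 0.00005625 = 631.4, so 632 against the stated 633.

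All 19 rows of Tables 3 and 4 reproduce within 3%, and 633 × 1.27 = 804. The sample size therefore matches a household-clustered design with five people per household. The planned totals agree: 8,000 people / (300 + 1,300) households = 5.

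**2. True size of the unadjusted test.** The design effect is D = 1 + (m − 1) × ICC, and the true size of a nominal 5% test is 2 × [1 − Φ(1.96/√D)]. The protocol gives no ICC for seroconversion, so a range is needed.

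*Low end, from the protocol's own k.* If k = 0.25 also held for seroconversion, ICC = k² × p/(1 − p), where p is the proportion seroconverting (assumed 5% or 20%):
- p = 0.05: 0.0625 × 0.05/0.95 = 0.003
- p = 0.20: 0.0625 × 0.20/0.80 = 0.016

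*Higher values, assumed:* ICC 0.05, 0.10 and 0.20.

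| ICC | D (m = 5) | True size | Effective sample per arm (804 × 5 = 4,020 people) |
| --- | --- | --- | --- |
| 0.003 | 1.013 | 5.2% | – |
| 0.016 | 1.06 | 5.7% | – |
| 0.05 | 1.20 | 7.4% | 3,350 |
| 0.10 | 1.40 | 9.8% | 2,871 |
| 0.20 | 1.80 | 14.4% | 2,233 |

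A beta-binomial simulation (804 households per arm, m = 5, 20,000 runs) agrees for the three assumed ICCs: 7.5%, 9.6% and 14.6% at 5% seroconversion, and 7.5%, 10.0% and 14.0% at 20%.

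**3. Village strata.** The chi-squared test also ignores village, and this works the other way. With arms balanced within villages, D is about 1 + (m − 1) × ICC(household within village) − ICC(village). For m = 5:
- household 0.05, village 0.10: D = 1 + 0.20 − 0.10 = 1.10, size 6.2%
- household 0.05, village 0.20: D = 1 + 0.20 − 0.20 = 1.00, size 5.0%
- household 0.02, village 0.10: D = 1 + 0.08 − 0.10 = 0.98, size 4.8%

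The p-values are thus too small unless the village component exceeds about four times the household component.

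**4. Fewer people at risk per household.** If people already seropositive at baseline are left out, m falls below 5. At ICC 0.10, m = 3 gives D = 1.20 and size 7.4%; m = 2 gives D = 1.10 and size 6.2%. The protocol gives no baseline seroprevalence.

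**The case against.** The strongest reply is that the inflation may be slight. The only clustering figure in the protocol, k = 0.25 (0.30 in two rows of Table 3), implies a size of about 5% to 6%. At 5% seroconversion, an ICC of 0.05 would need k of about 0.97 and an ICC of 0.20 about 1.95, roughly four and eight times the planning value. Unmodelled village strata and fewer at-risk members per household both reduce the inflation further.

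Much of this stands. It rules out a reading that the test must exceed its nominal level by a wide margin. The protocol fixes neither the household nor the village correlation, so too small is the expected direction and not a certainty. Nor do larger households add much: they may be enrolled, but the planned totals average exactly five.

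The reply does not rescue the test. The k was set for malaria, and nothing in the protocol shows that it applies to dengue, JE or scrub typhus. The plan adjusts malaria for household even with that k. If the household and village effects did cancel, that would be chance and not a property of the method.

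A reader might also infer that the trial's main result is in doubt. The text does not support that: the malaria and fever comparisons already carry a household random effect.

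**Conclusion.** Wrong as written. The chi-squared test on individuals does not match the household randomisation, and its p-values for the three seroconversion outcomes are likely too small. The true size of a nominal 5% test runs from near 5% to about 14%, given five people analysed per household, no village effect, and a household ICC between the value implied by the malaria k and an assumed 0.20. A village component, or fewer people at risk per household, lowers these figures. This should be fixed, but it concerns secondary outcomes only and leaves the primary conclusion, the sample size and the recruitment untouched.

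**What to change.** In Data Analyses and Handling, replace the chi-squared test for seroconversion with an analysis that allows for household clustering: logistic regression with a household random effect, generalised estimating equations with household-robust standard errors, or a cluster-adjusted chi-squared test. This applies the principle already adopted for malaria and fever.

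Account for village as well where the number of events allows. This goes beyond the stated malaria model, which names no village term. With 126 villages and possibly few events, a full set of village strata may be too sparse to fit.

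The cost is about one sentence, with no new data and no change to recruitment. Confidence intervals widen by √D: √1.013 = 1.01, or about 1%, at the low end and √1.80 = 1.34, or about 34%, at the high end. If household clustering proves negligible, the adjusted result will barely differ from the unadjusted one.
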